## Abstract

**Introduction:**

Despite therapeutic advances, many individuals with type 1 diabetes are unable to achieve tight glycaemic target without increasing the risk of hypoglycaemia. The objective of this study is to determine the effectiveness of a 3-month day-and-night home closed-loop glucose control combined with a pump suspend feature, compared with sensor-augmented insulin pump therapy in youths and adults with suboptimally controlled type 1 diabetes.

**Methods and analysis:**

The study adopts an open-label, multi-centre, multi-national (UK and USA), randomised, single-period, parallel design and aims for 84 randomised patients. Participants are youths (6–21 years) or adults (>21 years) with type 1 diabetes treated with insulin pump therapy and suboptimal glycaemic control (glycated haemoglobin (HbA1c) ≥7.5% (58 mmol/mol) and ≤10% (86 mmol/mol)). Following a 4-week run-in period, eligible participants will be randomised to a 3-month use of automated closed-loop insulin delivery combined with pump suspend feature or to sensor-augmented insulin pump therapy. Analyses will be conducted on an intention-to-treat basis. The primary outcome is the time spent in the target glucose range from 3.9 to 10.0 mmol/L based on continuous glucose monitoring levels during the 3-month free-living phase. Secondary outcomes include HbA1c at 3 months, mean glucose, time spent below and above target; time with glucose levels <3.5 and <2.8 mmol/L; area under the curve when sensor glucose is <3.5 mmol/L, time with glucose levels >16.7 mmol/L, glucose variability; total, basal and bolus insulin dose and change in body weight. Participants’ and their families’ perception in terms of lifestyle change, daily diabetes management and fear of hypoglycaemia will be evaluated.

**Ethics and dissemination:**

Ethics/institutional review board approval has been obtained. Before screening, all participants/guardians will be provided with oral and written information about the trial. The study will be disseminated by peer-reviewed publications and conference presentations.

**Trial registration number:**

NCT02523131; Pre-results.

Strengths and limitations of this studyThe study adopts a multi-centre, multi-national, randomised, parallel designThe study includes youth and adult participants across a wide range of age groups and geographical locationsParticipants in both study arms have equal numbers of study visitsThe study excludes participants who are hypoglycaemia unaware, living alone and those with HbA1c below 7.5% and above 10%The study is open-label, and the comparator does not include the use of pump suspend feature

## Introduction

Type 1 diabetes mellitus (T1D) is caused by an immune-mediated destruction of insulin-producing pancreatic beta-cells resulting in insulin deficiency.^1^ It commonly presents in childhood, but one-fourth of cases are diagnosed in adults. T1D accounts for 5%–10% of the total diabetes cases worldwide.^2^ The incidence of T1D is still increasing by around 3% every year, particularly among children.^2^ Around 86 000 children develop T1D each year, and in 2015, the number of children with T1D exceeded half a million for the first time.^2^

Despite rapid advancements in insulin delivery and the on-going development of more physiological insulin preparations,^3^ achieving optimal glycaemic control while avoiding hypoglycaemia remains a challenge for many people with T1D. The emergence of continuous glucose monitoring (CGM) over the last decade,^4 5^ which enables users to view real-time interstitial glucose readings and receive alarms for impending hypoglycaemia or hyperglycaemia, facilitating appropriate changes in insulin therapy, is a major step towards improved diabetes monitoring. Studies have shown the clinical benefit of CGM in reducing HbA1c with regular use of the device.^6^ Sensor-augmented pumps (SAPs) combine real-time CGM with insulin pump therapy, and studies have shown HbA1c reduction compared with multiple daily injection basal–bolus therapy.^7^ Automatic suspension of insulin delivery by the pump when a predefined threshold is reached (low glucose suspend feature) has been demonstrated to significantly reduce the burden of hypoglycaemia.^8^

The development of a closed-loop system that combines glucose monitoring with computer-based algorithm-directed insulin delivery^9^ may provide further improvements in glycaemic control while reducing hypoglycaemia^10 11^ and represents an emerging treatment option for people with T1D.^12^ Closed-loop differs from conventional pump therapy, characterised by preprogrammed basal delivery, through the use of a control algorithm that directs subcutaneous insulin delivery according to sensor glucose levels. People with T1D are known to have significant variability in daily insulin requirements,^13^ which may be addressed by closed loop.

Closed-loop studies have progressed from fully supervised research facility settings^14 15^ to remotely monitored transitional settings such as diabetes camp and hotel settings.^16 17^ The use of closedloop during unsupervised free living conditions over extended periods represents the ultimate testing bed within the target environment (table 1). The longest randomised day-and-night home study to date has shown benefit in glycaemic control with concurrent reduction of the risk of hypoglycaemia.^10^ On the basis of a recent non-randomised 3-month pivotal study,^12^ the US Food and Drug Administration (FDA) approved the insulin-only closed-loop system for use in clinical practice.^18^

**Table 1 T1:** Primary outcome of four randomised free-living unsupervised home day-and-night closed-loop studies

Study	Duration of home closed loop (days)	Population	Time spent in target (%)		p Value	Reference
			Closed loop	Control		
Dan04 phase 1	7	Adolescents	72	53	<0.001	Tauschmann *et al* 24
Dan04 phase 2	21	Adolescents	67	48	<0.001	Tauschmann *et al* 25
AP@home02	7	Adults	75	63	0.006	Leelarathna *et al* 23
AP@home04 phase 1	84	Adults	68	57	<0.001	Thabit *et al* 10
AP@home04 phase 2	28	Adults	76	66	<0.001	Bally *et al* 26

No study thus far has combined the pump suspend feature^8^ with closed-loop insulin delivery. In previous closed-loop systems, preprogrammed basal insulin rates are delivered in the event of communication failure between control algorithm device and the insulin pump. In the present closed-loop system, in-built pump suspend feature is immune to such communication failures and will operate even if the control algorithm device is not in range, reducing the risk of prolonged hypoglycaemia. Thus, the addition of pump suspend feature to a closed-loop system further increases user safety by discontinuing insulin delivery at low sensor glucose levels.

We plan to assess the efficacy, safety, utility and acceptability of a 3-month day-and-night home closed-loop glucose control combined with pump suspend feature in youths and adults under free-living conditions compared with SAP therapy.

## Methods and analysis

### Overview

This is an open-label, multi-centre, multi-national, randomised, one-period, parallel study contrasting day-and-night automated closed-loop glucose control combined with pump suspend feature (threshold suspend) to therapy during free-living home setting (figure 1, protocol version 5.0 dated 28 February 2017). Study participants will include youths and adults with suboptimally controlled T1D treated with insulin pump therapy. Recruited participants will be randomly assigned to 3 months of study intervention. The study will aim to randomise 84 participants stratified at study site, as appropiate, according to the two age groups, which will be based on the age of minors in the USA (equal proportions of youths (6–21 years) and adults (22 years and older)). The University of Cambridge (UK) and Jaeb Center (USA) will be the coordinating centres. Clinical sites include:

### Inclusion criteria

At least 6 years or older (with equal proportion of youths (6–21 years) and adults (22 years and older))T1D as defined by WHO for at least 1 year or confirmed C peptide negativeAn insulin pump user for at least 3 months, with good knowledge of insulin self-adjustment as judged by the investigatorTreated with one of the U-100 rapid-acting insulin analogues only (insulin aspart, lispro but not glulisine)Willing to perform regular capillary blood glucose monitoring, with at least four blood glucose measurements taken every dayScreening HbA1c ≥7.5% (58.5 mmol/mol) and ≤10% (86 mmol/mol) based on analysis from local laboratory or equivalentLiterate in EnglishWilling to wear CGMWilling to wear closed-loop system at homeWilling to follow study-specific instructionsWilling to upload pump and CGM data at regular intervalsWilling to restrict alcohol consumption to ≤2 units per day throughout the study periodFemale participants of child-bearing age should be on effective contraception and must have a negative urine-HCG pregnancy test at screeningLiving with someone who is trained to administer intramuscular glucagon and is able to seek emergency assistanceAccess to Wi-Fi at home.

### Exclusion criteria

Non-T1D including those secondary to chronic diseaseUsing real-time CGM on regular basis in preceding 3 monthsAny other physical or psychological disease likely to interfere with the normal conduct of the study and interpretation of the study results as judged by the investigatorUntreated coeliac disease, adrenal insufficiency or hypothyroidismCurrent treatment with drugs known to interfere with glucose metabolism, for example, systemic corticosteroids, non-selective beta-blockers and monoamine oxidase inhibitors, among othersKnown or suspected allergy to insulinClinically significant nephropathy (estimated glomerular filtration rate <45 mL/min) or on dialysis, neuropathy or active retinopathy (defined as the presence of maculopathy or proliferative changes) as judged by the investigatorAdults: one or more episodes of severe hypoglycaemia as defined by American Diabetes Association^19^ in preceding 6 months; youths: one or more episodes of severe hypoglycaemia during the previous 6 months (adults and adolescents: severe hypoglycaemia is defined as an event requiring assistance of another person to actively administer carbohydrates or glucagon or take other corrective actions including episodes of hypoglycaemia severe enough to cause unconsciousness, seizures or attendance at hospital; children: severe hypoglycaemia is defined as an event associated with a seizure or loss of consciousness)Random C peptide >100 pmol/L with concomitant blood glucose >4 mmol/L (72 mg/dL)Regular use of acetaminophenLack of reliable telephone facility for contactTotal daily insulin dose ≥2 IU/kg/dayTotal daily insulin dose <15 IU/dayPregnancy, planned pregnancy or breast feedingSevere visual impairmentSevere hearing impairmentSignificantly reduced hypoglycaemia awareness in participants aged 18 years and older defined by Gold score of >4Using implanted internal pace-makerMedically documented allergy towards the adhesive (glue) of plasters or unable to tolerate tape adhesive in the area of sensor placementSerious skin diseases (eg, psoriasis vulgaris, bacterial skin diseases) located at places of the body, which potentially are possible to be used for the localisation of glucose sensorCurrently abusing alcohol, illicit drugs or prescription drugsUsing pramlintide (symlin) or other commonly used hypoglycaemic agents including sulphonylureas, biguanides, DPP4 inhibitors, GLP-1 agonists, SGLT-2 inhibitors at time of screeningElective surgery planned that requires general anaesthesia during the course of the studyShift worker with working hours between 22:00 and 08:00Sickle cell disease or haemoglobinopathyRed blood cell transfusion or erythropoietin within 3 months prior to the time of screening or plans to receive red blood cell transfusion or erythropoiesstin during the course of study participationDiagnosed with current eating disorder such as anorexia or bulimiaPlans to use significant quantity of herbal preparations (use of over-the-counter herbal preparation for 30 consecutive days or longer period during the study) or significant quantity of vitamin supplements (four times the recommended daily allowance used for 30 consecutive days or longer period during the study), which may affect glucose metabolism and/or blood glucose levels during the course of their participation in the study.

### Study schedule

The study will consist of up to 11 in-clinic visits and 6 preplanned telephone/email contacts. Overview and key activities of the study visits are shown in tables 2 and 3, with both intervention periods lasting 3 months.

**Table 2 T2:** Schedule of study visits/phone contacts when the participant is randomised to day-and-night closed -loop combined with pump suspend feature (intervention group)

	Visit/contact	Description	Start relative to previous/next visit/activity	Duration, hours
	Visit 1	Recruitment visit: consent, HbA1c, screening bloods and questionnaires, urine pregnancy test	-	1–4
Training and run-in (4 weeks)	Visit 2	Insulin pump training and the initiation of study pump, competency assessment	Within 1–3 weeks of visit 1	3–4
	Visit 3	CGM training, initiation of CGM, weekly contact via phone/email, competency assessment	Within 3–7 days of visit 2	2–3
	Visit 4*	Review pump and CGM data, optimisation of treatment, compliance assessment, randomisation	After 4 weeks of visit 3	<1
	Contact	Qualitative interview (with a subset of participants/family members)	After randomisation but before visit 5	<1
CL + LGS intervention (3 months)	Visit 5	CL initiation at clinic/home: urine pregnancy test, CL and suspend feature training, competency assessment, HbA1c	Within 1 week of visit 4	2–6
	Visit 6*	Review use of study devices	After 24–48 hours of visit 5	<1
	Visit 7†	Review use of study devices	After 1 week of visit 5	<1
	Visit 8*	Review pump and CGM data	After 1 week of Visit 7	<1
	Visit 9*	End of first month: review pump and CGM data	After 2 weeks of visit 8	<1
	Visit 10*	End of second month: review pump and CGM data	After 4 weeks of visit 9	<1
	Visit 11	End of closed-loop treatment arm (3 months): HbA1c, complete questionnaires and follow-up qualitative interviews	After 4 weeks of visit 10	1–3

*Could be done via phone/e-mail in the UK. Follow-up by phone is mandatory in the USA only.

†Could be done via phone/e-mail in the UK. In-person visit mandatory in USA only.

CGM, continuous glucose monitoring; CL, closed loop; HbA1c, glycated haemoglobin; LGS, low glucose suspend.

**Table 3 T3:** Schedule of study visits/phone contacts when the participant is randomised to sensor-augmented pump

	Visit/contact	Description	Start relative to previous/next visit/activity	Duration, hours
	Visit 1	Recruitment visit: consent HbA1c, screening bloods and questionnaires, urine pregnancy test	–	1–4
Training and run-in (4 weeks)	Visit 2	Insulin pump training and the initiation study pump, competency assessment	Within 1–3 weeks of visit 1	3–4
	Visit 3	CGM training, initiation of CGM, weekly contact via phone/email, competency assessment	Within 3–7 days of visit 2	2–3
	Visit 4*	Review pump and CGM data, optimisation of treatment, compliance assessment, randomisation	After 4 weeks of visit 3	<1
SAP intervention (3 months)	Visit 5	SAP initiation at clinic/home: urine pregnancy test, SAP training, competency assessment, HbA1c	Within 1 week of visit 4	2–6
	Visit 6*	Review use of study devices	After 24–48 hours of visit 5	<1
	Visit 7†	Review use of study devices	After 1 week of visit 5	<1
	Visit 8*	Review pump and CGM data	After 1 week of visit 7	<1
	Visit 9*	End of first month: review pump and CGM data	After 2 weeks of visit 8	<1
	Visit 10*	End of second month: review pump and CGM data	After 4 weeks of visit 9	<1
	Visit 11	End of SAP treatment arm (3 months): HbA1c, complete questionnaires	After 4 weeks of visit 10	1–3

*Could be done via phone/e-mail in the UK. Follow-up by phone is mandatory in the USA only.

†Could be done via phone/e-mail in the UK. In-person visit mandatory in the USA only.

CGM, continuous glucose monitoring; SAP, sensor-augmented pump; HbA1c, glycated haemoglobin.

### Study training

Following written informed consent, participants will be trained on the use of study insulin pump (modified Medtronic 640G pump, Medtronic MiniMed, Northridge, California, USA) and CGM sensor (Enlite 3, Medtronic). For minors, parents/guardians will provide written informed consent, and written assent will be obtained from minors. Training will be performed in the presence of parents/guardians. The study insulin pump will be preprogrammed using participants’ usual basal settings, carbohydrate-to-insulin ratio and insulin sensitivity factor. Competency on use of study devices with the participant (cosignature of guardian will be required in US participants) will be formally assessed.

### Run-in period

There will be a minimum 4-week run-in period. Participants will be contacted once weekly by phone or email for troubleshooting purposes. At the end of the run-in period, study devices will be downloaded to assess adherence during the last 14 days (participants will be required to demonstrate at least 12 days’ use of CGM and use of at least 75% of bolus calculator for meal boluses for randomisation). Participants need to perform weekly downloads of study devices.

### Randomisation

Eligible subjects will be randomised using central randomisation software to the use of day-and-night closed-loop combined with pump suspend feature (threshold suspend) or to sensor-augmented insulin pump therapy. The randomisation will be stratified at each centre by the two age groups (equal proportion of youth (6–21 years) and adults (22 years and older)) and HbA1c groups (equal proportion of below and above 8.5% (69 mmol/mol)).

A subset of participants randomised to closed-loop will be invited to take part in an interview study led by an independent team of qualitative researchers at the University of Edinburgh. Participants will be interviewed before and/or at the end of the closed-loop study period.

### Home treatment period

All participants will be admitted to a clinical facility at the start of each treatment period and have blood tests performed for HbA1c. Females of child-bearing age will have urine pregnancy test on arrival.

### Day-and-night closed-loop combined with pump suspend feature

Participants will be trained on connection and disconnection of the closed-loop system and switching between closed-loop and usual pump therapy. Participants will be instructed on the use of low-glucose suspend functionality and settings. During closed-loop period, meal bolus will be delivered by the insulin pump based on carbohydrate estimation. Specific instructions during closed-loop related to exercise management, sick day rules, hypoglycaemia and hyperglycaemia management and technical troubleshooting will also be reviewed with the participants by the study team. Competency on the safe and effective use of the closed-loop system will be assessed by the study team; only those who demonstrate the same will be allowed to continue to the home study phase.

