### Sensor-augmented pump (SAP) therapy

Participants randomised to SAP therapy will receive training on the effective use of real-time CGM for optimisation of insulin therapy. During SAP therapy, participants will enter information related to carbohydrate content of the meals and premeal capillary glucose values into the bolus wizard of the insulin pump. Participants will be instructed not to activate threshold suspend (low-glucose or predictive low-glucose suspend features). Hypoglycaemia and hyperglycaemia alarms can be activated and personalised as per participants’ requirements.

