### Participant withdrawal criteria

The following prerandomisation withdrawal criteria will apply:Participant is unable to demonstrate safe use of study insulin pump and/or CGM during run-in period as judged by the investigatorParticipant fails to demonstrate compliance with study insulin pump and/or CGM during run-in period.

The following prerandomisation and postrandomisation withdrawal criteria will apply:Participants may terminate participation in the study at any time without necessarily giving a reason and without any personal disadvantageSignificant protocol violation or non-complianceAny severe hypoglycaemia event related to use of the closed-loop systemThree severe hypoglycaemia events unrelated to the use of the closed-loop systemDiabetic ketoacidosis (DKA) unrelated to infusion site failure and related to the use of the closed-loop systemDecision by the investigator or the sponsor that termination is in the participant’s best medical interestParticipant becomes pregnant during the study periodAllergic reaction to insulinAllergic reaction to adhesive surface of infusion set or CGM sensorIf patient continues to use pump suspend feature in the control group despite advice to the contrary.

Withdrawn participants due to reasons 4–12 will be invited to provide blood sample at the end of the planned study intervention for the assessment of HbA1c.

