### Statistical analysis

All analysis will be conducted on an intention-to-treat basis. Data from all randomised participants with or without protocol violation including dropouts and withdrawals will be included in the analysis. Data will not be truncated due to protocol deviations.

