#### Primary endpoint

The primary analysis will evaluate between group difference in the time (midnight to midnight) spent in the target glucose range from 3.9 to 10.0 mmol/L (70–180 mg/dL) based on sensor glucose levels during the 12-week free-living phase.

A 5% significance level will be used to declare statistical significance for the primary outcome comparison.

Mean (SD) for % time spent in the target range will be tabulated by treatment group. A linear model will be used to compare the difference between the two intervention arms, while adjusting for baseline % time spent in the target glucose range and random site effect. A 95% CI will be reported for the difference between the treatment groups based on the linear model. Normality of the residuals will be assessed. If the residuals have highly skewed distribution, then ranked normal score transformation of outcome data will be applied in the regression model. However, previous experience suggests that % time in target glucose range will follow an approximately normal distribution. A detailed analysis plan will be provided separately.

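### A competency check after randomisation bars those who fail it from the home phase, in the closed-loop arm only as written, and leaves them without primary-outcome data

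*Protocol article*

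**What the plan says.** All references are to the protocol article.

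- **Order of events.** Tables 2 and 3 (Study schedule) place randomisation at Visit 4: "Review pump and CGM data, optimisation of treatment, compliance assessment, randomisation". Visit 5 follows within 1 week. For the closed-loop arm it is described as "CL initiation at clinic/home: urine pregnancy test, CL and suspend feature training, competency assessment, HbA1c".
- **Consequence of failing, closed-loop arm.** The section on day-and-night closed-loop has the study team assess competency, and then "only those who demonstrate the same will be allowed to continue to the home study phase".
- **Control arm (sensor-augmented pump).** Table 3 lists the matching Visit 5: "SAP initiation at clinic/home: urine pregnancy test, SAP training, competency assessment, HbA1c". The section on sensor-augmented pump therapy describes the training ("Participants randomised to SAP therapy will receive training on the effective use of real-time CGM for optimisation of insulin therapy") but attaches no condition to entering the home phase.
- **Outcome window.** Under Primary endpoint, time in range is "based on sensor glucose levels during the 12-week free-living phase".
- **Analysis commitment.** Under Statistical analysis: "Data from all randomised participants with or without protocol violation including dropouts and withdrawals will be included in the analysis".
- **Follow-up after withdrawal.** Under Participant withdrawal criteria, those withdrawn for reasons 4 to 12 "will be invited to provide blood sample at the end of the planned study intervention for the assessment of HbA1c". Continued sensor wear is not mentioned. Failing the Visit 5 check is not listed by name as a reason for withdrawal.

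**The concern.** The check comes after allocation, in an open-label trial, and is judged by a study team that knows the arm. Its stated consequence falls on one arm only. The phase from which a participant is barred is the phase that supplies all of the primary-outcome data.

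If no sensor data are collected for those who fail, the closed-loop mean is calculated from a subset selected after randomisation, while the control mean is calculated from all who were allocated. Skill with the device could plausibly be related to glycaemic control, so this loss need not be random. The intention-to-treat comparison would then move some way towards the per-protocol comparison, which the article already plans as a separate analysis.

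An analysis plan can say how missing values are handled. It cannot recover 12 weeks of sensor readings that were never taken.

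**Working it through.** **1. The plan's own figure.** Inputs from Power calculation: difference 10 points, SD 14.5 points, two-sided alpha 0.05, power 85%. Equal allocation is assumed, as the ratio is not stated.

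n per arm = 2 × (1.960 + 1.036)² × 14.5² / 10² = 37.8, so 38 per arm and 76 in total. This reproduces the stated 76. The 84 randomised leave 84 − 76 = 8 for dropout (9.5%) and give 42 per arm.

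**2. Is the gate after randomisation?** Yes: Visit 4 comes before Visit 5 in both tables. The home phase runs from Visit 5, with Visits 7 to 11 spaced 1 + 1 + 2 + 4 + 4 = 12 weeks in each arm. The follow-up clock is therefore already common to both arms.

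**3. What data would a barred participant have?** Baseline sensor data from run-in, an HbA1c if taken at Visit 5, and possibly an end-of-study HbA1c by invitation. Sensor glucose in the 12-week home phase: none, on the stated procedures.

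**4. Size of the possible bias.** Let k of 42 closed-loop participants be barred, with f = k/42, and let the gap be the mean of those admitted minus the mean that the barred would have had. The observed closed-loop mean exceeds the mean of all allocated by

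bias = f × gap.

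Neither k nor the gap is in the document. Gaps of 10 (equal to the planned effect) and 14.5 (equal to the planning SD) are used for illustration. As an upper bound, suppose the gate removed exactly the lowest outcomes of a normal distribution: bias = 14.5 × φ(z_f)/(1 − f).

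| k of 42 | gap 10 | gap 14.5 | upper bound |
|---|---|---|---|
| 0 | 0 | 0 | 0 |
| 1 | 0.24 | 0.35 | 0.8 |
| 2 | 0.48 | 0.69 | 1.5 |
| 4 | 0.95 | 1.38 | 2.7 |

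**5. Effect on the test.** For k = 4, SE = 14.5 × √(1/38 + 1/42) = 3.25. If there were no true difference and the shortfall came from selection alone, biases of 0.95 and 1.38 would give a two-sided type I error of about 6.0% and 7.1% in place of 5% (13.3% at the upper bound). Power for a true 10-point effect with 38 and 42 participants would still be about 87% (normal approximation). The issue is bias, not power, although four such losses would use half of the allowance of eight.

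**The case against.** The strongest reply is that the article describes a risk that may never arise.

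- **Failures should be few.** Entrants have used a pump for at least 3 months. Before randomisation both arms must show at least 12 of the last 14 days of CGM use and bolus-calculator use for at least 75% of meal boluses, and must use the study pump and CGM safely. Nothing says that the Visit 5 assessment allows only one attempt. This stands. However, run-in tests pump and CGM use, not closed-loop use, so it cannot rule failures out.
- **The model adjusts for baseline time in range**, which would absorb part of any shortfall already visible at baseline. This also stands, and the figures above ignore it.
- **The asymmetry may come from condensing the protocol.** The control arm has the same visit and the same assessment, and the article's silence does not show that control participants who fail would proceed. This is fair: the asymmetry is in the stated consequence, not in the assessment.
- **Withdrawal could be covered** by the criterion on investigator or sponsor decision in the participant's medical interest, which carries the HbA1c invitation. This is so, but it brings no sensor data.
- **Handling of missing data belongs in the analysis plan.** That is true of the method. It does not answer the point that the stated rule prevents collection of the data.

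A reader might infer that the gate does remove the least able users and does bias the result. The document gives no failure rate and no link between competency and time in range, so it does not support that. A reader might also infer that the gate excludes people from the analysis and so contradicts the intention-to-treat statement. It bars entry to the home phase only; the trouble is that the statement cannot then be fulfilled for them. Nor does the withdrawal list class a failed closed-loop check as a reason for use only before randomisation: the criterion there concerns pump and CGM use in run-in.

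**Conclusion.** The point holds as a risk of one-arm selection after randomisation that the article does not reconcile with its commitment to analyse all randomised participants. It is not a demonstrated bias. Three conditions must all be met: someone fails the Visit 5 check, their home-phase sensor data are not collected, and they would have had lower time in range than those admitted. Under those conditions, with 2 to 4 of 42 failing and an assumed gap of 10 to 14.5 points, the tilt towards closed loop is about 0.5 to 1.4 points before any baseline adjustment. That is modest against a planned effect of 10. The point is still worth settling, because protection is cheap if arranged beforehand and the data cannot be recovered afterwards.

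**What to change.** Keep the safety gate. Reconcile the closed-loop section, the sensor-augmented pump section with Table 3, the withdrawal criteria and the Statistical analysis section, so that they state:

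1. whether failing the Visit 5 check has the same consequence in the control arm;
2. that a participant in either arm who fails it stays in follow-up, with study CGM data collected and uploaded over the same 12 weeks from Visit 5, and with the week-12 HbA1c;
3. that this participant is analysed in the arm to which they were randomised.

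How a participant is treated after a failed check is a clinical matter for the sponsor, and no rule is proposed here.

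The cost is about a paragraph of protocol text and sensors for a few participants. The estimated effect may be slightly smaller if some closed-loop participants never use the system. If nobody fails, the change costs nothing beyond the text.
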